**Study Day 1: The following tests will be performed:**

- DEXA (except 1-month post op)
- IV placed and labs drawn (blood for serum potassium, and for complete blood count, hematocrit, liver function tests, HGB A1c, homocysteine)
- Subject will be escorted to metabolic chamber for 24 hour stay. Collection of 24-hour urine will also begin.
- Blood samples taken hourly from 0730 to 2030 to measure various plasma factors associated with obesity.

**Study Day 2:**

- Subject escorted from chamber to study room
- IVs placed
- Euglycemic-hyperinsulinemic clamp is begun
- Stable isotope tracer studies for amino acid and fat kinetics begun
- Muscle/fat biopsies are performed about 1 hour after study begins
- Prior to basal sampling period and prior to high-insulin sampling period, subject will be placed on metabolic cart for ½ hour of breathing testing
- Subjects will be given activity monitors to wear for the week after the study (one on wrist and one on waist) along with SASE to mail them back
- At end of study, subject is fed and monitored for at least an hour to assure blood glucose stability

**Subject will have operation, with or without omentectomy, then repeat the above procedures 1-, 6-, 12, and 24-months later. Subjects may also be asked to repeat these procedures at 3, 4, and 5 years post-operatively.**

***Subjects who DO NOT participate in the metabolic chamber (the following procedures will be performed in the preoperative period and at 1-, 6-, 12-, and 24-months post-operatively, as well as 3, 4, and/or 5 years post-operatively, unless otherwise noted):***

**Pre-study and Study Day 0 are the same, except subject is requested to collect 24 hour urine at home and bring the bottle(s) with them when they check into the GCRC.**

**Study Day 1 is like Day 2 (clamp study day) above, except:**

- DEXA is performed this day (prior to clamp study)
- Initial labs are drawn this day

**Subject will have operation, with or without omentectomy, then repeat the above procedures 1-, 6-, 12, and 24-months later. Subjects may also be asked to repeat these procedures at 3, 4, and 5 years post-operatively.**

1. **Risks**

**List all adverse effects observed in animal studies, previous human studies, or laboratory observations. List the frequency expected for the side effects and a statement that there may be unknown or unanticipated adverse effects.**

- If subject is uncomfortable in enclosed, small spaces, the metabolic chamber may cause anxiety
- IVs may cause slight discomfort, swelling, bleeding, bruising, clotting, or infection
- In the event of an arterial line being placed, insertion of catheter may cause bleeding, bruising, nerve damage, or infection
- Rarely, the insertion of a needle into an artery or vein may cause damage to the artery or vein and a clot may develop.
- There is a small risk of low blood sugar
- Lidocaine (used for biopsies) may cause burning and/or local rash or irritation. There is also a risk of heart rhythm problems. Although rare, it is possible that lidocaine could cause a tingling feeling around the mouth, dizziness, blurred vision, drowsiness, confusion, and/or seizures.
- There is exposure to radiation (from DEXA and tritiated glucose) equivalent to 3 months of radiation from natural surroundings
- The muscle/fat biopsies may cause soreness, bruising, infection, nerve damage or a hematoma.
- Removal of the omentum may increase chances of bleeding and will increase time under anesthesia
- As with any medical treatment, there may be unknown or unforeseeable risks associated with taking part in this research study.

1. **Reporting of Adverse Events or Unanticipated Problems involving Risk to Participants or Others**

**Adverse event grading and attribution scale:**

A serious adverse event (AE) is defined as either fatal or life-threatening, requires inpatient hospitalization or prolongation of an existing hospitalization, results in persistent or significant disability/incapacity, is medically significant or requires intervention to prevent one or other of the outcomes listed above.

Grading scale for adverse event intensity:

- ***Mild:*** Discomfort noticed but no disruption of normal daily activity.
- ***Moderate:*** Discomfort sufficient to reduce or affect normal daily activity.
- ***Severe:*** Incapacitating with inability to work or perform normal daily activity.

Attribution scale for AE reporting:

- ***Probable:*** Adverse event is related to the procedures (insulin clamp, muscle biopsy, omentectomy), including pain, bleeding, perforation of contiguous organs, infection, and death, if death resulted from one of the aforementioned complications.
- ***Possible:*** Adverse event follows the procedures within a reasonable period (within 7 days), but may have been produced by the subject's clinical state or other factors.
- ***Remote:*** Adverse event does not follow the procedures within a reasonable period (more than 7 days) and could readily have been produced by the subject's clinical state or other factors.
- ***Unrelated:*** Adverse event is judged to be clearly due to extraneous causes and does not meet the above criteria.

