**Study Plan**

We propose a randomized study to evaluate changes in glucose, amino acid, and fatty acid metabolism at early and late stages after bariatric surgery. We will explore the mechanism(s) of changes in any of these substrates by examining alterations in the secretion and action of energy regulating peptides and of the inflammatory responses. Morbidly obese subjects will be divided into two groups with 150 participants in each arm; 75 Caucasian participants and 75 African American and Hispanics:

**Group I**: will undergo bariatric surgery (RYGB, VSG, AGB)

**Group II:** will undergo bariatric surgery (RYGB< VSG< AGB) combined with omentectomyThe study will include Caucasians, African Americans and Hispanics matched for BMI, gender and age. It will include short and long term aims with respect to the time after the surgical intervention in addition to the pre-operation basal period.

We will also obtain fat and muscle samples from normal weight individuals undergoing other abdominal surgery to serve as controls.

**Specific Aim 1: Determine the mechanism for the metabolic improvements after** bariatric surgery

Metabolic effects of the surgery will be examined at 4-weeks postoperatively, at a time when early improvements in insulin sensitivity are observed in the majority of Caucasian subjects and when changes in BMI or body composition are minimal. Subjects will also be studied at 6, 12 and 24 months when weight loss becomes significant. Subjects may also be asked to return at 3, 4, and 5 years post-operatively in order to continue to observe changes that occur in the long-term. We will evaluate which improvements following RYGB can be related to early alterations in specific energy-regulatory peptides and/or inflammatory factors and which simply follow the decrease in body weight.

**Specific Aim 2: Explore the mechanism for the blunted and delayed metabolic improvement after** bariatric surgery **in African Americans and Hispanics**

Comparison of the temporal changes in the metabolic profile will be made under matched experimental conditions for Caucasians, African Americans and Hispanics. Gene microarray analysis from two adipose tissue depots as well as skeletal muscle will be used to obtain an unbiased approach that will guide data interpretation.

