**Specific Aim 3: Explore whether combining omentectomy with bariatric surgery helps accelerate and sustain post-surgical metabolic improvements especially in the more refractory African American and Hispanic populations**

Removal of the greater omentum will be combined with bariatric surgery randomly in a subgroup of subjects. We hypothesize that onset time and magnitude of the metabolic improvements (as in **Specific Aim 1**) in African Americans and Hispanics who undergo bariatric surgery combined with omentectomy will be comparable to Caucasians undergoing bariatric surgery alone (without omentectomy). As already indicated, the African American cohort of patients manifested significantly improved insulin sensitivity to glucose metabolism. We seek to test the mechanisms of improvement and to uphold the null hypothesis that the two said groups are comparable over time. In all three aims, the studies proposed include determination of the following parameters:

1. Regional fat stores and muscle distribution by body circumference measurements and DEXA scans
2. Adipocyte size, tissue macrophage content and macrophage gene expression
3. Diurnal and food-induced secretion of adipokines such as leptin, resistin and adiponectin
4. Diurnal and food-induced secretion of the energy regulating-peptides such as ghrelin and PYY
5. Kinetics of blood glucose, amino acids and fatty acids
6. Insulin responsiveness and secretion
7. Levels of inflammatory markers such as CRP, IL-6, TNF-α2R (measure of TNF-α in plasma)
8. **Animal Studies and Previous Human Studies**

**Describe the process and outcome of the animal and/or laboratory studies that have been done. Also, if any previous human studies have been done (e.g., Phase I, other phases maybe in a different population or for a different indication).**

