**Day of Surgery:**

- Subject is met in pre-op area and told about study. Subject is asked if he/she would be willing to let surgeon take muscle and fat samples during the operation. If subject agrees, he/she is consented and surgeon is notified.

**Randomization:** The randomization schedule will be generated by statistical software. The randomization code will be generated using a permuted block size of four. No other restrictions will be used. As each subject is recruited, the randomization is assigned by the coordinator and the surgeon is notified. The PI, [name], will not be involved in the selection and allocation of patients. All recruited patients and researchers involved in the evaluation of the end-points will be blinded to the treatment assigned throughout the whole study period. No interim analyses will be carried out during the course of this study.

1. **Study Procedures**

**Provide a description of what the participants will experience. For example, a description of the instructions that will be given to the participants, activities in which they will engage, the length and timing of involvement, and the circumstances under which they will provide data (e.g., phone calls, spending time in an uncomfortable position, group assessments, one-on-one interview, videotaping, audiotaping, etc.)**

***Subjects who participate in metabolic chamber (the subjects will be assigned to the metabolic chamber in the preoperative period and will have chamber studies again at 6-, 12-, and 24-months post-operatively, as well as 3, 4, and/or 5 years post-operatively, unless otherwise noted):***

**Study Day 0:** Subject reports to the GCRC in the afternoon. The following are performed:

- Measurements of Height, Weight, and Body Circumferences.
- History and Physical Examination
- Performance of EKG (if over age 40)
- Performance of serum pregnancy test (if fertile female)
- Answer SF-36 Questionnaire
- Orders will be written for no food and caffeine after 20:00. They will be made completely NPO after 24:00

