**AE reporting:**

- All study-related mild and moderate adverse events will be evaluated by the Principal Investigator and/or the Safety Officer or sub-PI within 72 hours; serious AEs will be evaluated within 24 hours, and promptly as needed.
- Serious adverse events will be reported to Human Subjects/IRB no later than 10 days after becoming aware of the event.
- Annual reporting of adverse events will be conducted with the Human Subjects annual review/renewal according to their protocol.

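### The attribution scale lists omentectomy but not the bariatric operation both arms receive, so evaluation and follow-up of non-serious operative events can differ by arm

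*Protocol*

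**What the plan says.** **The arms.** Under Study Plan, Group I "will undergo bariatric surgery (RYGB, VSG, AGB"); Group II has the same choice of operations "combined with omentectomy". The plan is for "two groups with 150 participants in each arm"; the power section works with 33 + 33 = 66 per surgical group in the short-term phase.

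**The scale.** Under Adverse event grading and attribution scale, *Probable* reads: "Adverse event is related to the procedures (insulin clamp, muscle biopsy, omentectomy), including pain, bleeding, perforation of contiguous organs, infection, and death". *Possible* refers back to the same procedures: "Adverse event follows the procedures within a reasonable period (within 7 days"), with the proviso that the patient's clinical state or other factors may have been the cause. *Remote* is the counterpart: "Adverse event does not follow the procedures within a reasonable period (more than 7 days") and readily explained otherwise. *Unrelated* is for clearly extraneous causes.

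**What depends on attribution.** Under AE reporting, "All study-related mild and moderate adverse events will be evaluated by the Principal Investigator" and/or the Safety Officer or sub-PI within 72 hours. Under Safety Reports, study-related events are monitored until they resolve.

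**What does not.** Serious events are evaluated within 24 hours and go to the IRB within 10 days, with no condition of relatedness. The coordinator's quarterly reports cover any adverse event.

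**The concern.** The insulin clamp and muscle biopsy are done in both arms. Omentectomy is the only listed procedure that differs by arm, and the only listed one that belongs to the randomised operation. The complications named in the scale (pain, bleeding, perforation, infection, death) are ones that abdominal surgery in either arm could produce. Two patients with the same event on the day after surgery can therefore get different labels because of their allocation and not because of the event.

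The label has consequences. For mild and moderate events it decides whether the 72-hour evaluation applies and whether the event is followed to resolution. More scrutiny in one arm tends to give more complete information on harm in that arm. Bleeding is the harm most exposed: the Risks section already warns that removing the omentum may make it more likely, so it is the one the trial most needs to compare fairly. If anyone later tabulates related events by arm, or draws on them to judge harm under Study Withdrawal/Discontinuation, the comparison would lean against omentectomy even if omentectomy added no risk.

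**Working it through.** The protocol gives no figure to reproduce here. The check is to trace one event through the text in each arm.

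**Step 1: the same event, both arms.** Take a mild wound infection or minor bleed on day 1 after surgery.

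| Question | Group I (bariatric surgery) | Group II (bariatric surgery + omentectomy) |
|---|---|---|
| Does it follow a listed operative procedure? | No | Yes, omentectomy |
| Within 7 days of a listed procedure? | Only if the preoperative clamp or biopsy was that recent, or a biopsy was taken at surgery | Yes |
| Natural category | *Remote* or *Unrelated* | *Possible*, or *Probable* if judged due to omentectomy |
| 72-hour evaluation and follow-up to resolution if mild or moderate | Generally not required | Required if *Possible* or *Probable* counts as study-related |
| In the quarterly report | Yes | Yes |

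The next scheduled clamp and biopsy come about 4 weeks after surgery, so they cannot supply a listed procedure for a day-1 event in Group I.

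**Step 2: the same event, but serious.** Evaluation within 24 hours and the IRB report apply in both arms. There is no difference.

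**Step 3: how large could the labelling difference be?** The protocol states no operative complication rate, so the rates below are assumptions, equal in both arms. Suppose the extreme case: every such event is labelled related in Group II and none in Group I. The expected related count in Group II is n × rate, against 0 in Group I.

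| Assumed rate | n = 66 per arm | n = 150 per arm |
|---|---|---|
| 2% | 66 × 0.02 = 1.3 vs 0 | 150 × 0.02 = 3 vs 0 |
| 5% | 66 × 0.05 = 3.3 vs 0 | 150 × 0.05 = 7.5 vs 0 |
| 10% | 66 × 0.10 = 6.6 vs 0 | 150 × 0.10 = 15 vs 0 |

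If someone applied a two-sided Fisher exact test to related events, 6 vs 0 would be the smallest split with p < 0.05 at either arm size. With X ~ Binomial(n, rate), the chance of a spurious result is P(X ≥ 6):

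- n = 66, all Group II events labelled related: 0.112, 0.657 and 0.944 at rates of 5%, 10% and 15%.
- n = 66, half labelled related (effective rates 2.5%, 5% and 7.5%): 0.006, 0.112 and 0.375.
- n = 150, all labelled related: 0.766 at 5% and 0.998 at 10%.

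The full-labelling rows are upper bounds. The spread from 0.006 to 0.998 shows that the result is set by the assumed rate, the assumed labelling share and the arm size. It is not an estimate for this trial.

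**The case against.** **The list has a rationale.** Under Enrollment for morbidly obese patients, candidates are already approved for their operation. The bariatric procedure is clinical care; the clamp, biopsy and omentectomy are what the research adds. Limiting attribution to research procedures is defensible, and calling every complication of routine bariatric surgery study-related would be debatable. This stands as a reason to keep the scale. It does not remove the asymmetry: omentectomy is done within the same operation, so its complications cannot be cleanly separated from those of the bariatric step.

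**The consequential events are captured anyway.** This also stands. Many bleeds, infections and perforations would meet the protocol's definition of serious and are then handled alike in both arms. The gap is confined to non-serious events.

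A reader might infer more than the text supports:

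- *That a control-arm operative event can never be related.* Too absolute. Control patients also have the clamp and biopsy, the interval from the preoperative study to surgery is not stated, and a biopsy at surgery cannot be ruled out because the marks in the Table of Events are not legible in the text at hand. Nor is the Group II label automatic: *Probable* needs a judgement of relatedness, and the protocol does not say which categories count as study-related.
- *That the trial will produce a false signal of harm, or stop on one.* The statistical section plans no test of adverse events by arm, and no interim analyses are planned. The discontinuation criterion on evidence of harm does not mention attribution.
- *That attribution breaks the blind.* The randomization paragraph says "researchers involved in the evaluation of the end-points will be blinded to the treatment assigned throughout the whole study period", and also blinds patients. Adverse events are evaluated by the Principal Investigator, Safety Officer or sub-PI, and nothing says that adverse events are an end-point or that these assessors are among those blinded. No contradiction is shown.

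**Conclusion.** The point holds in a limited form. The attribution list is asymmetric by arm, and because two handling rules hang on study-relatedness, evaluation and follow-up of mild and moderate operative events can differ between Group I and Group II from the day of surgery. Any comparison restricted to related events would be biased against omentectomy. Serious events and the quarterly listing are untouched.

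This rests on two readings: that *the procedures* in *Possible* and *Remote* are the three named under *Probable*, and that at least *Possible* counts as study-related in practice. The direction of the bias follows from the text. Its size does not; the figures above are illustrations under assumed rates and a test the protocol does not plan. It is worth correcting because the correction is cheap and the harm comparison matters for an added surgical procedure.

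**What to change.** Keep the attribution scale for research procedures if that is wanted, and add two statements:

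1. In AE reporting and Safety Reports: all peri-operative adverse events after the index operation (bariatric surgery with or without omentectomy) are evaluated and followed to resolution in the same way in both arms, whatever their attribution.
2. Harm is compared between arms on all such events regardless of attribution, including where the Principal Investigator weighs evidence of harm under Study Withdrawal/Discontinuation.

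It would also help to say which attribution categories count as study-related.

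The cost is a few sentences of protocol text and somewhat more recording and evaluation of non-serious events in the control arm. No change to design, sample size or efficacy analysis is needed.

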**AE reporting:**

- All study-related mild and moderate adverse events will be evaluated by the Principal Investigator and/or the Safety Officer or sub-PI within 72 hours; serious AEs will be evaluated within 24 hours, and promptly as needed.
- Serious adverse events will be reported to Human Subjects/IRB no later than 10 days after becoming aware of the event.
- Annual reporting of adverse events will be conducted with the Human Subjects annual review/renewal according to their protocol.

**Safety Reports:**

- The study coordinator will produce quarterly administrative reports that describe study progress including accrual, demographics, and subjects’ status. Reports will also describe adherence to inclusion/exclusion criteria and study protocol, and any adverse events.
- Study-related adverse events will be monitored by the study coordinator, sub-investigators, or Principal Investigator, until resolved.
- The Principal Investigator and study coordinator will each be responsible for ensuring that adverse events are reported to the IRB and Safety Officer in compliance with their requirements.
- The Safety Officer as well as study physicians will be alerted if any unexpected serious (e.g., injury which requires medical treatment) adverse event occurs, to determine whether changes in the study protocol (e.g., additional safety measures, change in exclusion criteria) are needed.
- The Principal Investigator will notify the IRB for any changes needed to the protocol. In addition,
- The Principal Investigator will review all data collection forms on an annual basis for completeness and accuracy of the data, as well as protocol compliance, and a statement reflecting the results of the review will be sent to the NIDDK in the annual report and to the IRB at the time of Continuing Review.

1. **Study Withdrawal/Discontinuation**

**List the process for withdrawing from the study. List the process for being withdrawn from the study and the indications for withdrawal.**

**At any time, subjects may withdraw from the study (i.e., withdraw consent to participate) at their own request. A subject’s participation in the study may be discontinued at any time at the discretion of the Investigator and in accordance with his/her clinical judgment. No disadvantage will arise for any subject who withdraws consent for participation at any time or who is withdrawn from the study by the Investigator.**

Reasons for discontinuation of study treatment will be recorded on the appropriate page of the CRF in any case and may include the following:

- Subject's request for withdrawal
- Investigator's decision that discontinuation is in the best interest of the subject
- Non-compliance with the regimen and timing that might result in dropping out from the study
- Development of an intolerable adverse event due to study participation as determined by the Investigator, subject, or both.
- Development of an intercurrent illness, condition, or procedural complication, which would interfere with the subject's continued participation.
- Subject is lost to follow-up

**If a subject fails to return for a scheduled visit, a documented effort must be made to determine the reason. This information should be recorded in the study records.**

Based on IRB recommendations, any adverse event that is identified and has not been addressed in the consent form must be added. The Principal Investigator will discontinue implementation of a protocol for the following reasons:

- There is clear evidence of harm or harmful side effects of the treatment or procedure;
- In the event that a serious adverse event occurs that increases the risk to participants, the study will be stopped and an investigation will be conducted and a findings report generated to the investigators, IRB, and the NIDDK;
- There is overwhelming evidence of the benefit of the treatment versus the control arm.

1. **Statistical Considerations**

**Describe the statistical power of the study, the confidence intervals and the method for analysis. Describe any possible deviations and their statistical impact.**

***Statistical Analysis:*** This protocol will provide information regarding basal carbohydrate, lipid and amino acid metabolism. Insulin sensitivity of hepatic glucose production will be determined using the 0.6 mU/kg.min insulin infusion rate. Peripheral glucose utilization will be determined using the 2.0 mU/kg.min insulin infusion rate *(Bonadonna 1990)*. The study will also provide information regarding insulin sensitivity of fatty acid metabolism (lipolysis and re-esterification). Studies in obese subjects and type 2 diabetic subjects demonstrated a right shift in the rates of insulin-stimulated suppression of lipolysis, hepatic glucose production and stimulation of peripheral glucose uptake. The insulin levels required were most sensitive for suppression of lipolysis followed by suppression in glucose production and then by insulin of stimulated glucose uptake *(Matthaei 2000)*.

***Statistical Methods, Sample Size, and Power Estimates:*** We based sample size estimates on historical case volumes (>600 procedures per year), patient demographic distributions (70% Caucasian, 25% African American, 5% Hispanic, 80% female 20% male). Persons who consent to participate will be enrolled in both the short and long term phases of the study. We assumed attrition for the short-term phase, which entails data points through postoperative week four, to be negligible, and for the long-term study, which entails a two-year postoperative follow-up period, to be ~ 25% by postoperative month 24. We based this rate on reported attrition following bariatric surgery over a comparable time, and the rate is assumed to be comparable between experimental groups. Anticipated effect sizes were based on previous research or standard conventions for large, medium, and small effects *(Cohen 1988)*. Unless noted, power estimates were determined using standard methods and software (Power and Precision™ v. 2.0, nQuery Advisor™ v. 3.0) for non-directional tests at the 0.05 alpha level.

Demographic information such as age, race, and gender will be tabulated. Descriptive statistics, including means, standard deviations, and ranges for continuous measures, as well as percentages and frequencies for categorical measures will be presented. Statistical analyses will be performed using standard packages (SPSS or SAS).

**Specific Aim 1:** The short-term phase of the investigation will include a group of 66 Caucasians and group of 66 African Americans and Hispanics (each of the two groups randomized to 33 bariatric surgery and 33 bariatric surgery + omentectomy). The long-term phase of the investigation will include at least 100 patients (25 in each of the four racial and procedure groups).

Initial analyses will examine the short-term effects of race and surgical procedure (bariatric surgery + omentectomy), and the interaction effect of race by surgical procedure on change in measures of body composition, inflammatory factors, hormones, energy-related peptides, and health-related quality of life following bariatric surgery. The general case statistical method is mixed-model repeated measures analysis of variance with tests of: (a) the within-subjects effect of time; (b) the between-subjects main effects race and surgical procedure; and (c) race by procedure by time interaction effects. Simple contrasts will be used to test effects at postoperative week four in relation to preoperative measure. Statistical tests of main and interaction effects of race and omentectomy on any contrast are analogous to interaction of these effects with the within-subject change scores (simple contrasts). Assuming a within-subject correlation between longitudinal data points that is as low as 0.35 in the combined sample (n=132), power is adequate (85%) to detect a small effect (d=0.3) of time for any contrast. Power to detect, for any contrast, medium (f=0.30) overall main effects of race and omentectomy and the race by omentectomy interaction effect is 92%. This statistical design will also be applied within each racial group (n=66) to more explicitly examine the effect of omentectomy, and within each surgical group (n=66) to more explicitly examine the effect of race. For these analyses, the power to detect medium to large (d=0.70) effects for any contrast is 80%.

The long-term data, which entails five data points (preoperative, 1 month, 6 months, 12 months, and 24 months). Mixed effects modeling will be employed to determine whether patterns of individual change in outcome measures vary due to race, surgical procedure (bariatric surgery + omentectomy), and clinical covariates. Advantages of this method are that: (a) data from individuals with missing data may be included providing that the point(s) can be considered ‘missing at random’; (b) between-subject variation in the timing of assessment points can be accommodated (i.e. time is treated as a continuous variable); and (c) continuous or discrete time-sensitive covariates (e.g. weight loss, syndrome X symptom expression) can be incorporated. Follow-up analyses will be conducted on the sample having complete data through month 24 (expected n=100, 25 in each of four unique race by surgical procedure conditions) using methods described above for the short-term phase of the investigation. Simple and repeated contrasts will be employed to test within-subjects effects of time in relation to the preoperative measurement and the preceding time point, respectively. Assuming a within-subject correlation as low as 0.45, power is adequate (83%) to detect a small effect (d=0.3) of time on any contrast. Power to detect, for any contrast, medium (f=0.30) overall main effects of race and omentectomy and the race by omentectomy interaction effect is 84%. The power to detect large (d=0.81) effects of surgical procedure within each racial group (and of race within each surgical procedure group) for any contrast is 80%.

**Specific Aim 3:** Analyses addressing **Specific Aim 3** will be performed using the statistical methods described above for both the short and long term phases of the investigation (mixed-model repeated measures analysis of variance and mixed effects modeling). Two subject groups will be included in these analyses: (a) African American and Hispanic patients receiving bariatric surgery plus omentectomy, and (b) Caucasian patients receiving bariatric surgery without omentectomy. Our hypothesized mechanism for the effects of omentectomy and race implies that these two groups will experience comparable outcomes over time. Given our previous data, which demonstrated a large effect of race (d > 1.5) on weight reduction following bariatric surgery, and our hypothesis that omentectomy will blunt the disparity in African Americans and Hispanics, effect sizes were set at > 0.81. The power to detect an effect of group (d=0.81) on a within-subject contrast (change over time) in the short-term phase of the study (33 patients per group) is 90%. Power is 80% to detect a comparable effect (d=0.81) on any contrast in the long-term study (minimum group size = 25). In order to analyze the effect of omentectomy independent of race, a sample size of 11 participants per group would allow us to detect a 25% difference in insulin sensitivity between groups, with an *alpha* value of 0.05 and power of 80% (*beta* = 0.2). This is based on data on glucose kinetics obtained previously in obese participants (Klein 2004). A difference of this magnitude is clinically meaningful because it represents the lower end of the observed effect of current treatment strategies for insulin resistance, such as moderate weight loss (Kelley, 1993; Kirk 2009; Tiikkainen 2004; Ross 2000) and thiazolidinedione therapy (Schrauwen-Hinderling 2008; Li 2007; Coletta 2009) which increase hepatic and skeletal muscle insulin sensitivity by 25-50%.

1. **Privacy/Confidentiality Issues**

